#### Sessions in the DOT Group

The auditor will score the daily compliance weekly based on the booklet photos sent by the TB patients and their observers. The patients will be considered to have daily compliance as reported (no audit). The auditor will make a phone call to the TB patients to confirm if they were observed as reported by their observer and to remind them to safely store the booklet and all zipped bags received from the TB clinic. If the patients report that they were not observed, the auditor will further investigate and record the observer’s actions such as making phone calls instead of in-person visits to check patients’ daily drug administration, missing patient appointments, or performing activities not included in the in-person DOT protocol.

A daily session reported by the observer will be scored as 1 for daily compliance as confirmed by the patients and 0 otherwise. If a patient misses a phone call twice or loses the booklet and/or the blank zipped bags, they will be discontinued from the intervention and their daily scores of the previous 7 days will be 0. All scored sessions will be recorded in the DOT record system of the server. The activities of observers not included in the in-person DOT will also be recorded.

### Follow-ups

Each patient will be scheduled to return to the TB clinic for a follow-up on the 61st day. One day before the scheduled visit, the TB nurse will remind the patient in the DOT group to return the booklet and zipped bags. A deep-cough specimen will be collected early in the morning for 3 consecutive days. The sputum specimens will then be sent for an AFB test. The patients will be requested to notify their doctors about all adverse events occurring from the start of the treatment. The doctors will record the reported adverse events in the electronic health record (EHR) system and suggest appropriate treatment. If a patient misses their follow-up appointment, the responsible TB nurse will contact them and record the reasons in the EHR.

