##### DOT for Patients

For patients in the DOT jurisdiction, the TB nurse will provide a booklet for recording daily drug intake and whether the intake is observed by the assigned observer. The TB nurse will request the patients to return the booklet and all zipped bags on the follow-up day to claim their compensation. Each weekend, the auditor will notify the patients to capture and send the most recent page of the booklet to the official LINE chat, to which the observers do not have access.

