#### Secondary Outcomes

The clinical outcomes retrieved from the EHR, conversion of the AFB smear (three negative sputum smears as mentioned above), reporting of adverse events, missing the follow-up visit, and death during the 60-day follow-up period will be compared between the two groups.

For adverse events, information retrieved from the EHR system will be used to compare the reporting of adverse events by the observers in both the VOT and DOT groups.

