### Statistical Analysis

Background information of patients and observers will be summarized using descriptive statistics.

An intention-to-treat analysis will be performed according to the randomized allocation. Thus, participants will be classified according to the intervention group to which they are assigned, regardless of their actual intervention.

We will compare the percentages of compliance between the two interventions at 60 days after treatment initiation. The 60-day compliance of the individuals will be defined as the percentage calculated using the following formula: (mean cumulative compliance days×100)/60. Our study is a cluster randomized controlled trial; thus, the cumulative number of compliant days of patients and observers will be nested in clusters. We will analyze their 60-day compliance considering that the same observer may monitor more than one patient. The intervention effect will be based on a linear mixed-effects model [22]. According to our study design, the intervention will be a fixed effect, whereas the cluster level will be a random effect.

The number of compliant days of patients and their observers will be visualized using solid green dots indicating the daily compliance of the individual subjects (Y-axis) and the elapsed number of days since starting the medication (X-axis). To investigate the dynamics of compliant days of the patients and observers over time, the mean cumulative number of complaint days within each group will also be plotted. The estimation of mean cumulative compliant days will range between 0 and 60, with 60 indicating that all participants in the group completed their daily sessions for 60 days. The function will be plotted using the mean cumulative number of compliant days (Y-axis) and the elapsed number of days since the start of medication administration (X-axis). Ideally, a steady increase in linear trend with a 45° slope indicates 100% compliance at any point from 0 to 60 days. Flattening of the slope represents a decline in the compliance percentage over time within the group.

Only descriptive statistical methods will be used on the aforementioned clinical outcomes and noncompliance activities of the observers because we may not have sufficient statistical power to detect small differences.

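### The nurse contact on the day before the day-61 visit is described for DOT patients only, although missing that visit is an outcome compared between arms

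*Protocol article*

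**What the plan says.** Under Follow-ups, the visit applies to both arms: "Each patient will be scheduled to return to the TB clinic for a follow-up on the 61st day". The next sentence applies to one: "One day before the scheduled visit, the TB nurse will remind the patient in the DOT group to return the booklet and zipped bags". Sputum is then described without reference to arm: "A deep-cough specimen will be collected early in the morning for 3 consecutive days". So is the contact after a missed visit: "If a patient misses their follow-up appointment, the responsible TB nurse will contact them and record the reasons in the EHR".

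Under DOT for Patients, the hand-in is tied to payment: "The TB nurse will request the patients to return the booklet and all zipped bags on the follow-up day to claim their compensation".

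The Secondary Outcomes section includes "conversion of the AFB smear (three negative sputum smears as mentioned above"), adverse-event reporting, and "missing the follow-up visit, and death during the 60-day follow-up period will be compared between the two groups". All are retrieved from the electronic health record. The Statistical Analysis section limits how they are handled: "Only descriptive statistical methods will be used on the aforementioned clinical outcomes and noncompliance activities of the observers".

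**The concern.** Attendance on day 61 is an outcome, and a contact on day 60 about bringing items to that visit is likely to affect attendance. The article gives this contact to the DOT arm and describes no counterpart for VOT. The VOT notifications (Background of the Existing A-VOT in Thailand; VOT for Observers) concern the daily drug-taking session, not the clinic appointment.

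The contact is not part of what the trial sets out to compare. The DOT intervention is home-visit observation by the primary care unit observer. This contact comes from the TB clinic nurse and serves the recovery of record-keeping materials. If fewer DOT patients miss the visit, the trial could not tell whether the observation method or the nurse's call was responsible. The smear results and the adverse events that doctors record at follow-up depend partly on the same attendance, so their completeness may differ between arms too.

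**Working it through.** **Which follow-up steps depend on arm.** Taking the Follow-ups section step by step:

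- Day-61 visit: every patient.
- Day-60 nurse contact: DOT group only.
- Three morning sputum specimens: no arm restriction.
- Request to report adverse events to the doctor: no arm restriction.
- Nurse contact after a missed appointment: no arm restriction.

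The only arm-specific step is the one that comes immediately before attendance is measured. The contact after a missed appointment cannot prevent the miss, though it may recover some data.

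**Possible size.** The article states no attendance, reminder-effect or conversion figure, so there is nothing to reproduce, and every rate below is an assumption.

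*Missed visits.* Let p be the proportion missed in VOT and r the relative reduction from the contact in DOT. The artificial gap is p × r.

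- Smallest case: p = 5%, r = 30%. Gap = 0.05 × 0.30 = 1.5 points.
- Middle case: p = 10%, r = 50%. Gap = 0.10 × 0.50 = 5 points.
- Largest case: p = 20%, r = 50%. Gap = 0.20 × 0.50 = 10 points.

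The Sample Size section gives 57 patients per arm before inflation and 70 after. The range therefore runs from about 1 patient (57 × 0.015 = 0.9) to 7 patients (70 × 0.10).

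*Sputum conversion, with missing counted as not converted.* With the same true conversion c in both arms, the artificial gap in favour of DOT is c × p × r.

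- c = 75%, p = 5%, r = 30%: 0.75 × 0.015 = 1.1 points.
- c = 85%, p = 20%, r = 50%: 0.85 × 0.10 = 8.5 points.

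*Sputum conversion, complete cases only.* Suppose 80% of patients attend in any case and convert at 85%. The contact brings in a further 10% in DOT, who convert at rate m. VOT then shows 85%, and DOT shows (0.80 × 0.85 + 0.10 × m) / 0.90.

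- m = 50%: 0.730 / 0.90 = 81.1%, so DOT minus VOT = −3.9 points.
- m = 80%: 0.760 / 0.90 = 84.4%, so −0.6 points.
- m = 85%: 0.765 / 0.90 = 85.0%, so 0.
- m = 95%: 0.775 / 0.90 = 86.1%, so +1.1 points.

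The sign depends on how patients who would otherwise have missed the visit differ from the rest, and on how missing results are handled.

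*Adverse events.* Fuller attendance in DOT would tend to put more events on record there. That could make DOT look worse, or better at reporting, depending on how the reader takes it.

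**After the change.** With the same contact in both arms, r is equal across arms and each of these artificial gaps becomes 0 under the same assumptions.

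**The case against.** The strongest reply is that the sentence concerns returning materials and names the DOT group because only those patients have a booklet and bags to return. Routine appointment reminders may exist in both arms, since Cointerventions keeps TB clinic care as in routine practice apart from the assigned intervention. This stands in part. A reader might infer that VOT patients receive no reminder at all, but the article does not say so. Even if an unstated routine reminder exists, however, DOT patients as described get an additional contact on day 60.

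A reader might also infer that sputum and adverse-event results are biased toward DOT. The documents do not support that. The sputum effect can go either way, more recorded events need not favour DOT, and the clinic visit is not the only route for adverse events: VOT patients note them daily and patients in either arm can phone the clinic.

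Nor can payment be called an attendance incentive for DOT alone. Cointerventions lists the completion payments for all patients. What is specific to DOT is the condition of handing items in, and this could also deter patients who have lost them. Its net direction is not established.

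VOT patients do have frequent contact of other kinds: daily notifications, the LINE chat and calls after a late video. These concern dosing. They make the net effect on attendance less certain, but they do not remove the difference in the pre-visit contact.

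Finally, these outcomes are secondary, no test is planned, and the Introduction says significant differences are not expected. That limits the consequence. It does not remove the distortion, because raw percentages by arm will still be read as a comparison.

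**Conclusion.** The point holds in a limited form. The plan as written gives one arm a prompt on the day before an attendance outcome is measured, and this can lower missed visits in DOT for a reason unrelated to the observation method. Completeness of sputum and adverse-event data may also differ between arms, in an uncertain direction.

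The size is unknown. The range of 1.5 to 10 points for missed visits rests entirely on assumed rates (5% to 20% missed in VOT, a 30% to 50% reduction in DOT). The primary outcome, compliance over the 60 days, is not affected, so the superiority conclusion does not depend on this. It is an avoidable asymmetry worth removing because doing so is cheap.

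**What to change.** Amend Follow-ups so that the TB nurse contacts every patient in both arms on day 60 with the same message about the visit and the sputum specimens, by the same route, and adds the request for the booklet and bags for DOT patients only. If VOT patients already receive an equivalent contact, one sentence saying so is enough.

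The cost is one short message or call per VOT patient, about 57 to 70 in total, made by the existing nurses. No new staff or data collection is needed.

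For any patients already followed up under the current procedure, the report should state that the pre-visit contact was described for DOT only, and should show the number with sputum results by arm beside the conversion percentages.

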### Data Collection

Data regarding observational activities will be recorded in the database, and data regarding clinical outcomes will be documented in the EHR system of the involved hospitals. These records will be retrieved for analysis at the end of the follow-up.

### Outcomes

#### Primary Outcomes

Data recorded by the auditor will be compiled to understand the compliance of patients and observers in each arm. For compliance of the individual TB patients, the daily compliance scores rated by the auditor will be summed and divided by 60 (for the 60 days of observation) to obtain the percentage of cumulative days with compliance. For the whole group of patients, the mean cumulative number of compliance days will be calculated, taking the clusters into account.

Similarly, for compliance of the individual observers, the daily compliance score rated by the auditor will be calculated. The individual compliance unit of an observer will be the number of days each patient is actually observed. A higher number of patient doses observed will increase the overall contribution of the observer to the mean cumulative number of compliance days for the whole group of observers (VOT or DOT).

#### Secondary Outcomes

The clinical outcomes retrieved from the EHR, conversion of the AFB smear (three negative sputum smears as mentioned above), reporting of adverse events, missing the follow-up visit, and death during the 60-day follow-up period will be compared between the two groups.

For adverse events, information retrieved from the EHR system will be used to compare the reporting of adverse events by the observers in both the VOT and DOT groups.

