#### Cluster Level

##### VOT for Observers

To avoid a learning curve on the VOT side, the observers will be trained to demonstrate to the patient on how to correctly record and approve the recorded video according to the SOP [7]. They will be required to undergo real or simulated activities for 1 month before the trial [9].

After being notified about patient recruitment, the observers will visit patients at home on the first day. They will confirm whether the patient can record the video according to the SOP [7]. The observer and the patient will set an appointment time for medication administration. Next, the patient will keep a daily record of the drug-taking session, note any adverse events, and send the video to the observer through the TH VOT system. The observer will review the video, approve the session, and provide any necessary advice through the LINE chat box. The observer will follow up with a phone call if the patient fails to send the video within 30 minutes of the appointment.

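### The secondary outcome attributes adverse-event reports in the EHR to observers, but the only described route into the EHR is patients telling doctors

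*Protocol article*

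**What the plan says.** Secondary Outcomes first lists the reporting of adverse events among the clinical outcomes taken from the EHR and compared between groups. It then adds, specifically for adverse events, that "information retrieved from the EHR system will be used to compare the reporting of adverse events by the observers" in the VOT and DOT groups.

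Follow-ups describes how adverse events come to be in the EHR. In connection with the day-61 clinic visit, "The patients will be requested to notify their doctors about all adverse events occurring from the start of the treatment", and then "The doctors will record the reported adverse events in the electronic health record (EHR) system and suggest appropriate treatment".

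Data Collection separates the two stores: "Data regarding observational activities will be recorded in the database, and data regarding clinical outcomes will be documented in the EHR system".

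On what happens between visits, VOT for Observers says that, using TH VOT, "the patient will keep a daily record of the drug-taking session, note any adverse events, and send the video to the observer". DOT for Patients says that "the TB nurse will provide a booklet for recording daily drug intake and whether the intake is observed by the assigned observer". Cointerventions lets patients or their families in either arm phone the TB clinic about a suspected adverse event.

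**The concern.** The outcome names one reporter (the observer) and a data source whose described content comes from another (the patient, through the doctor). An analyst who follows Secondary Outcomes would extract adverse events from the EHR and label them as observer reporting. A reader would then take the result as evidence on how well VOT and DOT observers pick up and pass on adverse events, which these data do not show.

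This matters because the trial is about observer performance as well as patient compliance, and the Conclusion says that a superior result would lead the authors to advocate replacing DOT with VOT. A statement that observers in one arm reported more, or as many, adverse events could carry weight in that argument. It should rest on data about observers.

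A second, smaller issue concerns interpretation. Daily noting of adverse events is described for VOT patients and not for DOT patients. Even a correctly labelled count of patient reports at day 61 could be influenced by that difference.

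**Working it through.** No arithmetic applies. The plan gives no figure for this outcome, and the point does not depend on alpha, power or sample size. The check is to follow each described route for adverse-event information and see where it ends.

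1. **Patient to doctor to EHR (Follow-ups).** Both arms, same visit on day 61, same request to the patient, entry by the doctor. This is the only route that the article states as ending in the EHR. The observer plays no part in it.

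2. **Patient or family to TB clinic by phone (Cointerventions).** Both arms. No EHR entry is stated. If these calls are entered, they are still reports from patients or families, not from observers.

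3. **VOT patient to observer (VOT for Observers).** The patient notes adverse events with the daily session and sends the video through TH VOT. The observer may give advice through the chat. No onward step to a doctor or to the EHR is described. Data Collection would place this material in the study database.

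4. **DOT patient to observer (DOT for Patients, DOT for Observers, Sessions in the DOT Group).** The booklet is described as covering drug intake and whether it was observed. The weekly photographs and the auditor's calls concern the same matters. No adverse-event item is described.

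5. **Observer compliance criteria (Sessions in the VOT Group, Sessions in the DOT Group).** None mentions reporting an adverse event, so the auditor's scores do not supply the missing observer report either.

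Set side by side:

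| Quantity | VOT | DOT | In the EHR? |
|---|---|---|---|
| Patient tells doctor, day-61 visit | described | described | yes |
| Patient or family phones clinic | described | described | not stated |
| Patient notes event to observer | described, daily | not described | not stated |
| Observer reports event onward | not described | not described | not stated |

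The outcome in Secondary Outcomes is the last row. The source it names is described as holding the first row. The two do not match in either arm.

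The first row is the same in both arms. Any effect of daily noting on EHR counts must therefore act indirectly, for example if a VOT patient who has noted events during treatment recalls more of them at day 61. The document allows that possibility but gives no means of sizing it.

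**The case against.** The strongest defence is that this is one loose phrase. The first sentence of Secondary Outcomes, and the statement of objectives in the Introduction, list the reporting of adverse events without naming observers. That outcome can be obtained from the EHR. This stands: an adverse-event outcome is measurable, and only its attribution to observers is not supported.

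One could also read the EHR as a reference against which observers' own reports are checked. That reading does not rescue the sentence, because no collection of observer adverse-event reports is described for DOT.

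Several stronger readings are tempting, and the document does not support them:

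- **That EHR capture itself differs by arm.** The visit, the request to patients, the doctor's entry and the clinic phone line are the same for both groups. Only an indirect effect through recall is plausible.
- **That the DOT booklet has no place for adverse events.** The article states the purpose of the booklet and does not list all its fields. It is a condensed account, and its silence does not show that the field is absent.
- **That this is the trial's only safety comparison.** Death during the 60 days is also compared.
- **That a spurious difference of a given size can be expected.** This would need capture rates for each arm, and the article gives none.

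Finally, the consequences are modest. Statistical Analysis restricts clinical outcomes to descriptive methods, and the Introduction says that significant differences in secondary outcomes are not expected. That also stands, and it limits how much weight the point should carry.

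**Conclusion.** The point holds as a mismatch between an outcome and its data source. The sections state who reports, who records and where the data are kept, and they disagree on the reporter. It is therefore not a detail left to a fuller document.

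The effect is on what the comparison can be said to show. EHR data as described support a statement about adverse events that patients reported to doctors. They do not support one about reporting by observers. A between-arm difference in those counts should be read with the caveat that daily noting is described for VOT only and may have aided recall.

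The size is limited and not quantifiable from the document: the outcome is secondary and descriptive, and the primary compliance comparison is untouched. The conclusion assumes that the routes described in the article are the ones used. If observers' reports are in fact passed to doctors and identifiably entered in the EHR in both arms, stating that route would resolve the mismatch.

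**What to change.** 1. In Secondary Outcomes, define the EHR outcome as adverse events reported by patients to doctors by the day-61 visit, and delete *by the observers*.
2. Report adverse events noted to observers as a separate descriptive summary for VOT, taken from the TH VOT session records. Compare them between arms only if an equivalent DOT record was collected from the start.
3. State, next to the outcome or under Limitations, that daily noting of adverse events is described for VOT only, that it may indirectly raise recall at day 61, and that a between-arm difference in EHR counts may therefore partly reflect ascertainment.

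The cost is a few sentences and an export of existing TH VOT records. Adding an adverse-event column to the DOT booklet now is not advisable. Results says that recruitment began in January 2022, so a new column would change DOT ascertainment part-way through the trial and create a further inconsistency.
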